**7.3 Documentation and evaluation of side effects**

**(See also Appendix B, pages 14 to 16)**

The severity of side effects is classified according to the NCI v.3.0 criteria. All side effects and all therapies administered for their treatment are recorded in the patient documentation and in the eCRF. If side effects are still present at the second study visit, they are tracked until they disappear (by telephone if medically justifiable). SAEs are also listed on a special SAE form. Whether there is a correlation with the study medication is assessed as described in Appendix B, point 4.3.

**7.4 Notification of adverse events and annual safety report**

**(See also Appendix B, pages 17 to 35)**

The Principal Investigator as investigator/sponsor of the study ensures that all SAEs and SUSARs are reported to him/her by the study team, usually on the same day. He ensures that an authorised and competent deputy is always available in case of absence.

Life-threatening and fatal SAEs are immediately reported to the Cantonal Ethics Committee (CEC). The remaining SAEs are summarised in an annual safety report for the attention of the CEC Berne. Serious Adverse Drug Reactions (SARs) and SUSARs are reported to the Cantonal Ethics Committee and Swissmedic in accordance with official guidelines. The exact procedure is described in Appendix B, point 4.5.3.

**7.5 Pregnancy**

Every woman of child-bearing age has to undergo a urine pregnancy test before enrolment. Pregnant women cannot be included in the study. All women of childbearing age are required to prevent conception for at least three weeks. If no permanent (medicinal or mechanical) contraception is used, temporary contraception with a mechanical method (condom) is required.

At the second study visit, specific questions are asked as to whether a pregnancy has become known in the meantime (a pregnancy test is not carried out). If this is the case, the outcome of the pregnancy will be inquired from every woman after she has given birth and the outcome is recorded in the eCRF.

**8. Power analysis and statistics**

The main endpoint of the intervention study is the difference in the mean level of fatigue on the numerical rating scale between the ferinject and placebo groups four to six weeks after infusion of the study drug. Based on empirical values from the literature, a standard deviation of the fatigue values of 2.5 points can be assumed. A mean difference of one point on the scale is considered clinically relevant.

200 subjects per group lead to a power of >95% to detect such a reduction with a two-sided α error of 0.05. For a secondary analysis this number of cases leads to a power of about 85% to detect a statistical interaction of the treatment effect with a subgroup in the order of 1.5 points. The primary stratification criterion will be the ferritin value at baseline (<25 µg/l versus ≥25 µg/l). Secondary stratification criteria will be sex and fatigue at baseline (<4 versus ≥4 on the numerical rating scale).

The mean values on the numerical rating scale will be compared by means of covariance analysis between the groups corrected for baseline value of the numerical rating scale. For stratified analyses we will perform an interaction test using least squares regression models. All analyses will be performed according to the intention-to-treat principle, including all randomized patients in the group to which they were initially randomized. Any missing values are replaced by multiple imputation. In a sensitivity analysis only subjects with complete data are included. All P-values are two-sided. The data analysis is performed under blind conditions, i.e. the statistician in charge will not know which of the two groups analysed received iron and which placebo. All analyses are performed in Stata Release 11 (StataCorp, College Station, TX).

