**4.6 Randomization and Blinding in the Intervention Study**

The participants are randomized to the verum or placebo group in a 1:1 double-blind ratio. Stratification is performed according to the ferritin value at screening (≤25 μg/l or >25 μg/l), gender and the degree of pre-existing fatigue (<4 points versus ≥4 points on the numerical rating scale). Randomisation and stratification is carried out by the nurses of the Clinical Investigation Unit using the computer of the study database.

Since the placebo and the verum preparation differ in colour, the preparation and administration of the infusion must be carried out by an external person who is not otherwise involved in the care of the subjects. This task is performed by nurses from the Clinical Investigation Unit (CIU) of the Inselspital. The nurses of the CIU randomize the participants on the computer, bring the prepared infusion to the blood donation center and administer it. With the help of black colored infusion tubes and by covering the infusion bag with cloths, it is ensured that neither the test person nor the staff of the blood donation center can find out the study arm. Iron carboxymaltose is associated with slightly more frequent side effects compared to placebo^24^. Especially gastrointestinal complaints and general symptoms have been described. However, the extent of these side effects is so small that they will not have any relevant influence on blinding and thus statistical significance.

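### The primary covariance analysis omits ferritin stratum and sex, two of the three randomisation factors; if they are prognostic beyond baseline fatigue, the test is slightly conservative

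*Protocol*

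**What the plan says.** Protocol section 4.6 sets out 1:1 randomisation with three stratification factors: "Stratification is performed according to the ferritin value at screening" (25 µg/l or below against above 25), then "gender and the degree of pre-existing fatigue" (below 4 against 4 or more on the rating scale).

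Section 8 repeats the three factors and ranks them: "The primary stratification criterion will be the ferritin value at baseline", and "Secondary stratification criteria will be sex and fatigue at baseline". In that section the ferritin split is below 25 against 25 or more.

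For the primary comparison, section 8 says the group means will be "compared by means of covariance analysis between the groups corrected for baseline value of the numerical rating scale". No other covariate is named. The strata reappear only for the subgroup questions: "For stratified analyses we will perform an interaction test using least squares regression models". Nothing elsewhere in the protocol adds ferritin or sex to the primary model.

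**The concern.** Stratified allocation makes the arms more alike on the stratification factors than chance would. If those factors predict the outcome, the treatment estimate varies less from trial to trial. A model that omits them leaves their contribution in the residual variance and so reports a standard error larger than the true one. Intervals come out too wide and the test runs below its nominal level.

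The fatigue factor is already covered, because the continuous baseline score carries at least as much information as the split at 4. Ferritin, which section 8 ranks first, and sex are not covered. The protocol does not leave the covariate set open for a later document; it states a model. The interaction models, written in the usual way with stratum main effects, would then adjust for factors that the primary model ignores.

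What is at stake is a correctly sized standard error, and a primary model fixed in advance, so that no choice between adjusted and less adjusted results arises later.

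**Working it through.** **Inputs.** From section 8: 200 per group, two-sided alpha 0.05, "a standard deviation of the fatigue values of 2.5 points can be assumed", and "A mean difference of one point on the scale is considered clinically relevant". Assumed, because the protocol gives no figure: R², the share of the variance remaining after baseline fatigue that ferritin and sex explain, taken as 2%, 5% and 10%. Also assumed: allocation is balanced within strata.

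**The plan's own figures.** SE = 2.5 × √(2/200) = 0.25. Power = Φ(1/0.25 − 1.96) = Φ(2.04) = 97.9%, which agrees with the stated power above 95%. For the 1.5-point interaction with four equal cells of 100, SE = 2.5 × √(4/100) = 0.50 and power = Φ(1.5/0.50 − 1.96) = 85.1%, which agrees with the stated figure of about 85%. Neither figure is in question.

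**Effect of the omission.** With balance within strata, true SE = reported SE × √(1 − R²). Hence:

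- excess of the reported SE = 1/√(1 − R²) − 1
- actual alpha = 2 × [1 − Φ(1.96/√(1 − R²))]
- power, planned model = Φ((1 − 1.96 × 0.25)/true SE) = Φ(0.51/true SE)
- power, strata added = Φ(1/true SE − 1.96)

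The power columns keep 0.25 as the reported SE, that is, they take no credit for correlation between baseline and final fatigue.

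| Assumed R² | True SE | Reported SE too large by | Actual alpha | Power, planned | Power, strata added |
|---|---|---|---|---|---|
| 0% | 0.2500 | 0% | 5.0% | 97.9% | 97.9% |
| 2% | 0.2475 | 1.0% | 4.8% | 98.0% | 98.1% |
| 5% | 0.2437 | 2.6% | 4.4% | 98.2% | 98.4% |
| 10% | 0.2372 | 5.4% | 3.9% | 98.4% | 98.8% |

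The largest power difference is 0.4 percentage points. With an assumed baseline-to-final correlation of 0.5, all the powers exceed 99.6% and the differences are below 0.1 points.

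**Check by simulation.** 6,000 trials per setting, 400 participants, eight strata, blocks of 4 (block size assumed), correlation parameter 0.5, ferritin and sex each split evenly, no treatment effect:

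| Effect of ferritin and of sex | Mean reported SE, planned | True SE, planned | True SE, strata added | Type I error, planned | Type I error, strata added |
|---|---|---|---|---|---|
| none | 0.216 | 0.217 | 0.217 | 4.8% | 4.7% |
| 0.5 point each | 0.219 | 0.216 | 0.216 | 4.7% | 5.0% |
| 1 point each | 0.227 | 0.219 | 0.219 | 4.3% | 5.2% |

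Simulation error on a rejection rate is about √(0.05 × 0.95/6000) = 0.3 percentage points, so only the last row differs clearly from 5%. The mean error of the treatment estimate was below 0.005 point in every setting. The true SE is practically the same under both models; only the reported SE differs.

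To translate R² into points: a factor split evenly with an effect of b points has variance b²/4, and the remaining variance here is 6.25 × 0.75 = 4.69. Two effects of 0.5 point give 0.125/(4.69 + 0.125) = about 2.6%. Two effects of 1 point give 0.5/(4.69 + 0.5) = about 9.6%. The 10% case therefore needs ferritin and sex each to shift final fatigue by about the trial's whole clinically relevant difference, beyond what baseline fatigue already shows.

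**The case against.** The strongest reply is that a covariance analysis on the baseline score is a valid primary analysis and that the harm is very small. That is right: the error is in the conservative direction and the stated power is untouched.

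The prognostic premise is also open to doubt. What counts is variance explained after fatigue measured on the same scale some weeks earlier, and stable differences by sex or iron status will largely be in that score already. Section 2.3 itself finds no clear evidence linking iron deficiency in donors to symptoms, and sections 3.3.3 and 4.3.2 use sex and ferritin to define subgroups, not as predictors of fatigue. This stands, and it is why the size can only be given as a range starting at nil. On the other side, section 3.4 hypothesises that slight iron deficiency impairs general condition, so ferritin cannot be dismissed as a predictor.

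The result also needs restricted allocation within strata, and section 4.6 names no blocking or similar method. Without it, the planned test would hold its 5% level, and adding the factors would bring a true gain in precision: at R² = 10%, power of 98.8% against 97.9%, still under 1 point.

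A reader might infer that the benefit of stratifying is lost, or that the omission amounts to discarding 8, 20 or 40 of the 400 participants (400 × R²). The documents do not support that. Discarding participants raises the true standard error; this omission does not. The equivalence holds only for the width of the reported interval.

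**Conclusion.** The omission is a stated choice in section 8, not a detail left open, and the model would be better with the two factors in it. The severity is minor. Over an assumed residual R² of 2% to 10%, and with balanced allocation within strata, the reported standard error is about 1.0% to 5.4% too large and the actual two-sided alpha is about 4.8% to 3.9%. If ferritin and sex add nothing to baseline fatigue, nothing changes. The treatment estimate is unbiased and the sample size needs no revision. It would be wrong to conclude that the primary test is invalid or that false positives are inflated. The direction of the effect is certain under its conditions; its size rests on an R² that the protocol does not give.

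**What to change.** First reconcile the ferritin stratum. Section 4.6 uses the screening value, 25 µg/l or below against above 25; section 8 uses the baseline value, below 25 against 25 or more. These may be different measurements, since section 4.5.1 has ferritin determined again at the first study visit, four to six weeks after the donation, and a value of exactly 25 falls on opposite sides of the two splits. Until this is settled, a ferritin stratum as randomised has no single meaning.

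Then state the primary model in section 8 as second-visit fatigue score on treatment, continuous baseline fatigue score, sex, and the ferritin stratum actually used for randomisation. Carry the same terms into the imputation model and the complete-case sensitivity analysis, so that all three rest on the same covariates.

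The cost is the correction of the stratum definition and one sentence on the model. All the variables are collected before infusion, and neither the sample size nor the visits change. The change should be made before the data are analysed.

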**5.2.1 Inclusion criteria**

- Participation in the overview study

- Donation suitability

- At least one previous blood donation

- Signed declaration of consent

- Serum ferritin ≤50.0 μg/l

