**6. Measurements**

**6.1 Survey study**

**6.1.1. Questionnaire**

Each participant is asked to complete a questionnaire. This questionnaire consists of 14 questions and evaluates the following topics:

- Previous donor behaviour (2 questions)

- Pre-existing anemia (2 questions)

- Subjectively perceived fatigue (numerical rating scale from 1 - 10)

- Physical performance (numerical rating scale from 1 - 10)

- Concentration ability (numerical rating scale from 1 - 10)

- Loss of drive (numerical rating scale from 1 - 10)

- Depressive mood (Two numerical rating scales from 1 - 10)

- Hair Loss

- Changes in fingernails

- Fatigue caused by blood donation (2 questions)

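### Fatigue is rated on a 1-10 scale twice before treatment, but the primary covariance analysis corrects for one baseline value that is not tied to a visit; adding the survey score would be a cheap improvement

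*Protocol*

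**What the plan says.** Protocol section 8 fixes the primary model: mean fatigue scores are "compared by means of covariance analysis between the groups corrected for baseline value of the numerical rating scale". Subgroup effects are tested by interaction terms in least squares regression, and missing values are multiply imputed. No imputation predictors are listed.

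Two pre-treatment ratings are planned:

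- **Survey, at the screening donation.** Section 6.1.1 lists the item "Subjectively perceived fatigue (numerical rating scale from 1 - 10", and section 5.2.1 makes "Participation in the overview study" a condition for entering the trial.
- **Visit 1.** Under sections 4.5.1 and 6.2.1 the questionnaire booklet, with its own 1-10 fatigue rating, is completed after consent, four to six weeks after the donation.

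Section 8 does not say which of these is the baseline value. The word is used loosely there: the ferritin stratifier is called a baseline value in section 8 and a screening value in section 4.6. Section 4.6 also stratifies on pre-existing fatigue without naming the score.

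The sample size in section 8 rests on an SD of 2.5, a relevant effect of 1 point and a two-sided level of 0.05. On these it claims "200 subjects per group lead to a power of >95% to detect such a reduction". Elsewhere in the same section it gives "a power of about 85% to detect a statistical interaction of the treatment effect with a subgroup in the order of 1.5 points" for the secondary analysis.

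**The concern.** The primary outcome is a single self-rated item, so one reading is a noisy measure of a person's usual fatigue. Two pre-treatment readings can predict the final score better than one, and a better prediction reduces the residual variance of the treatment comparison. Both readings precede allocation, so adjusting for both does not bias the randomised comparison or change the effect being estimated.

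What is at stake is precision, chiefly in the interaction tests. These have the lowest planned power in the protocol, subgroup effects are named secondary endpoints (section 4.3.2), and finding a lower iron-store limit is a project aim (section 1). The survey score could also help to impute a missing visit-1 or final score.

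Leaving baseline undefined is a smaller matter of its own. If the survey score turned out to be the fatigue stratifier, a model adjusted only for visit 1 would leave that score out.

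**Working it through.** **Inputs from section 8:** SD 2.5, difference 1 point, 200 per group, two-sided 0.05, interaction 1.5 points. The correlations below are assumptions, because the protocol gives none.

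**The plan's own figures.**

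- Main effect: SE = 2.5 × √(2/200) = 0.25. Power = Φ(1/0.25 − 1.96) = Φ(2.04) = 97.9%, consistent with the stated figure of more than 95%.
- Interaction, equal halves, 100 per cell: SE = 2.5 × √(4/100) = 0.5. Power = Φ(1.5/0.5 − 1.96) = Φ(1.04) = 85.1%, matching about 85%.

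Both reproduce with the full SD, before any gain from baseline adjustment.

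**Equal correlation r among survey, visit-1 and final scores.** The residual variance factor is 1 − r² with one baseline and 1 − 2r²/(1 + r) with two.

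| r | One baseline | Two baselines | Variance reduction | Equivalent n per arm | Power, 1 point | Power, 1.5-point interaction |
|---|---|---|---|---|---|---|
| 0.3 | 0.910 | 0.862 | 5.3% | 211 | 98.7% → 99.1% | 88.2% → 89.8% |
| 0.5 | 0.750 | 0.667 | 11.1% | 225 | 99.6% → 99.8% | 93.4% → 95.7% |
| 0.7 | 0.510 | 0.424 | 17.0% | 241 | 99.99% → above 99.99% | 98.7% → 99.6% |

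Example at r = 0.5: the interaction SE goes from 0.5 × √0.75 = 0.433 to 0.5 × √0.667 = 0.408. For an interaction of 1.0 point, which is not a protocol target, power would go from Φ(1/0.433 − 1.96) = 64% to Φ(1/0.408 − 1.96) = 69%.

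**Survey score the weaker predictor.** Let a = correlation of visit 1 with final, q = survey with visit 1, u = survey with final. Then R² = (a² + u² − 2aqu)/(1 − q²). With a = q = 0.5 the single-baseline residual is 0.75, and:

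| u | Residual with both | Variance reduction |
|---|---|---|
| 0.4 | 0.720 | 4.0% |
| 0.3 | 0.747 | 0.4% |
| 0.25 (first-order decay, u = a × q) | 0.750 | 0% |

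For u = 0.4: R² = (0.25 + 0.16 − 0.20)/0.75 = 0.28. The 1.5-point interaction power is then Φ(1.5/(0.5 × √0.72) − 1.96) = Φ(1.58) = 94.2%, against 93.4% with visit 1 alone.

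**The case against.** The strongest case against is that nothing here is wrong. Covariance analysis on one baseline is valid, the stated powers reproduce, and additional covariates are often left to a statistical analysis plan. That stands, and it is why this is offered only as an improvement. Section 8 does, however, name the primary model and its covariate, so commenting on that choice is fair.

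The equal-correlation figures may also be optimistic. The survey rating is taken at a whole blood donation, which section 2.1 says removes 180 to 250 mg of iron, and visit 1 follows that loss. With visit 1 four to six weeks later and the final visit six to eight weeks after infusion (section 4.5.2), the survey score lies 10 to 14 weeks before the outcome. A weaker correlation with the final score is plausible, so the range has to include zero gain.

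A reader might infer more than the protocol supports:

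- *That the analysis explicitly uses the visit-1 score.* This is the natural reading, but section 8 does not say so.
- *That every participant will have scored the same item twice.* Survey participants are asked to fill in the questionnaire, and a completed fatigue item is not an entry condition. The topic and the 1-10 range match, but identical wording is not shown.
- *That the imputation leaves the survey score out.* Section 8 lists no predictors, so it neither includes nor excludes it.

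The change has costs. Some survey scores will probably be missing, and the planned complete-data sensitivity analysis could shrink. Section 11.1 promises anonymity of survey data. However, section 5.2 has survey participants selected by their ferritin and telephoned, so survey results must already be traceable to individuals for recruitment.

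**Conclusion.** The point holds as a cheap efficiency improvement. Two pre-randomisation fatigue ratings are planned, and the stated primary model corrects for one, without naming the visit. Using both would cut the variance of the treatment effect by about 5% to 17% under equal correlations of 0.3 to 0.7, by about 4% with correlations of 0.4 (survey) and 0.5 (visit 1) with the final score, and by nothing under first-order decay. All of these correlations are assumed.

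It would be tempting to conclude that the trial is discarding guaranteed precision or is short of participants. The documents do not support that: the gain may be nil, and primary power is already about 98% before any baseline adjustment. In the equal-correlation cases shown, primary power rises by less than half a percentage point. The practical benefit, if any, lies in the interaction and subgroup tests and possibly in the imputation. The planned single-baseline analysis remains valid.

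**What to change.** In section 8:

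1. Define the baseline fatigue value as the visit-1 score.
2. Prespecify the survey fatigue score as a second covariate in the primary covariance analysis and in the interaction models.
3. Include the survey score in the imputation model, and impute it where it is missing so that no participant is lost from the primary analysis.
4. State whether the complete-data sensitivity analysis requires the survey score, since requiring it may reduce that set.

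The cost is a sentence or two of text, a link from the survey item to the trial record that respects the anonymity commitment in section 11.1, and one degree of freedom. No new data are collected and the effect being estimated is unchanged.

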**Aim of the project:**

- Detailed description of the iron deficiency problem in a large group of blood donors.
- Clarification of the link between low iron stores and potentially related complaints, especially fatigue.
- Definition of a lower iron storage limit in blood donors, above which somatic and psychological complaints occur.
- Proof of the effectiveness of intravenous iron substitution and thus formal proof of the connection between iron deficiency and symptoms.
- Proof of the safety of intravenous iron substitution in blood donors.

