**11.2 Intervention study**

Iron carboxymaltose (Ferinject®) has a very favourable side-effect profile^28^, the most common being injection site reactions. Mild headaches, gastrointestinal complaints and skin rashes are also observed. Anaphylactic reactions, as feared with earlier intravenous iron preparations, are a great rarity with Ferinject®. The blood donation centre in Berne is also well prepared to treat such complications. The dose of iron carboxymaltose was selected so that, although the iron stores are sufficiently filled in each participant, iron overload with long-term toxic damage cannot occur at the same time. It is not to be expected mathematically that the serum ferritin will exceed the upper laboratory norm after reaching a state of equilibrium. In summary, the potential risks of the study drug are very low.

Half of participants will receive iron substitution, the other half placebo only (0.9% NaCl). Although it is now common practice for many doctors to substitute iron deficiency without anaemia, the risk of iron deficiency is very low. But this is not based on scientific data. From the point of view of evidence-based medicine, there is therefore no proven advantage neither for a person in the placebo group nor for one in the verum group.

After completion of the intervention study, each participant is informed in writing whether he or she has received the iron supplement or the placebo. In addition, the laboratory results of the first study visit and the ferritin value will be sent to the participants at the final visit. This information allows the treating family doctor to continue to treat the patient correctly.

The study promises very relevant results both for patients and healthy blood donors with iron deficiency without anaemia. The lower limit of the ferritin level above which iron must be substituted could be more precisely defined, thus enabling unnecessary iron infusions to be avoided in the future. If adverse effects of iron deficiency on blood donors can be demonstrated, blood donation procedures would need to be adapted. This would benefit all blood donors in the long term. Based on all of these considerations, the general medical benefit of the study justifies the very low risk for the individual study participant.

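### The split at ferritin 25 µg/l can show that the effect differs across 25 but cannot locate a limit; add a continuous-ferritin interaction and effect curve beside it

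*Protocol*

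**What the plan says.** Protocol section 8 makes ferritin the primary stratification criterion, in two classes divided at 25 µg/l, and adds "For stratified analyses we will perform an interaction test using least squares regression models". For 200 per group it states that "this number of cases leads to a power of about 85% to detect a statistical interaction of the treatment effect with a subgroup", for an interaction of about 1.5 points. The same two classes appear in the secondary question (3.3.3), the secondary endpoint (4.3.2) and the randomisation strata (4.6). No continuous ferritin term, second cut or effect curve is named. Ferritin is measured as a number in every participant at screening (6.1.2) and at both study visits (6.2.2), and eligibility ends at 50 µg/l (5.2.1).

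Two places speak of a ferritin limit:

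- Section 11.2, within the justification of the intervention study: "The lower limit of the ferritin level above which iron must be substituted could be more precisely defined".
- Section 1, among the aims of the whole project: "Definition of a lower iron storage limit in blood donors, above which somatic and psychological complaints occur".

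The survey part also bears on the second of these, since it relates complaints to iron parameters (3.2, 4.3.1).

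**The concern.** A two-class interaction compares two averages. It can say that the mean effect of iron below 25 differs from the mean effect above 25. It carries no information on where, within either class, the effect appears or disappears. Section 11.2 nevertheless offers a sharper limit for substitution as a benefit of the randomised study, and only the randomised comparison tests substitution.

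Two things are at stake. A significant interaction may be taken as support for 25 as the limit, and a non-significant one as evidence that no limit exists, when neither follows. And if the benefit changes gradually with ferritin, collapsing it to two classes gives up power on data already collected.

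**Working it through.** **Inputs.** From section 8: SD 2.5 points, 200 per group (400 in all), two-sided alpha 0.05, interaction 1.5 points. From section 4.6: 1:1 allocation. Assumed, because the protocol does not give them: the distribution of ferritin up to 50 among those enrolled, and the shape of the treatment effect over ferritin. Adjustment for baseline fatigue would shrink every standard error below by the same factor and leaves the information ratios unchanged.

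**1. The protocol's own figures.** Main comparison: SE = 2.5 × √(2/200) = 0.25, z = 1/0.25 = 4, power 97.9%, which agrees with the stated figure of more than 95%. Interaction with equal classes (four cells of 100): SE = 2.5 × √(4/100) = 0.50, z = 1.5/0.50 = 3, power = Φ(3 − 1.96) = 85.1%. The stated 85% reproduces. It needs near-equal classes: 83.6% at 40:60, 78.5% at 30:70, 73.8% at 25:75.

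**2. Can the split locate a limit?** Assume ferritin uniform from 5 to 50 and a true step: benefit 1.5 points up to the step, none above it. The share at or below 25 is 20/45 = 0.444, so SE = 2.5 × √(4/177.8 + 4/222.2) = 0.503.

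| True step at | Mean effect ≤25 | Mean effect >25 | Contrast | z | Power of split |
|---|---|---|---|---|---|
| 15 | 1.5 × 10/20 = 0.75 | 0 | 0.75 | 1.49 | 32% |
| 20 | 1.5 × 15/20 = 1.125 | 0 | 1.125 | 2.24 | 61% |
| 25 | 1.5 | 0 | 1.5 | 2.98 | 85% |
| 30 | 1.5 | 1.5 × 5/25 = 0.3 | 1.2 | 2.39 | 66% |
| 35 | 1.5 | 1.5 × 10/25 = 0.6 | 0.9 | 1.79 | 43% |

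Steps at 20 and at 30 give contrasts of 1.125 and 1.2, which an SE of 0.50 cannot separate. A significant result fits limits on either side of 25, and a null result does not exclude one.

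**3. Information kept if the effect is graded.** When the effect is linear in ferritin (or log ferritin), the split keeps a fraction r² of the information, the squared correlation of that variable with the class indicator. For a uniform distribution r² = 3q(1 − q), with q the share at or below 25.

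- Uniform 0–50, linear: q = 0.50, r² = 0.75
- Uniform 10–50, linear: q = 0.375, r² = 0.70
- Log-uniform 10–50, log-linear: r² = 0.74
- Log-uniform 5–50, log-linear: r² = 0.63
- Normal split at its median, linear: r² = 2/π = 0.64

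An interaction sized so that the split has z = 3 (85% power) has z = 3/r with the continuous value. That is 3.46 (93.4%) at r² = 0.75 and 3.77 (96.5%) at r² = 0.63. Equivalently, the split works as if 400 × 0.75 = 300 or 400 × 0.63 = 252 participants were used. Other assumed distributions with a log-linear effect fall lower, to about 0.49 at the extreme.

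**4. The reverse case.** For a true step at 25 with uniform 5–50, the split has z = 2.98 (85%). A linear term has z = 2.98 × √0.741 = 2.57, power 73%.

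**5. What a curve could show.** The overall effect has a 95% half-width of 1.96 × 0.25 = 0.49, and a curve is less precise at any one value. With uniform 5–50 and a three-knot spline, the half-width is about 0.7 to 0.8 points in mid-range, 0.95 at 10 and 1.4 at 50, against the 1 point that section 8 calls clinically relevant.

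**The case against.** The split answers the question the protocol poses. Sections 3.3.3 and 4.3.2 ask about improvement in named subgroups, and section 8 tests those subgroups with a power that is correctly stated. Neither section lists locating a limit as a question or endpoint of the intervention study. That stands, and it is why the split should stay.

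A reader might infer that the trial promises to define a ferritin limit by this test. The documents do not say so. The aim in section 1 belongs to the whole project and concerns where complaints occur, which the survey also addresses. Section 11.2 says only that the limit could be sharpened. But the survey does not test the effect of giving iron, and section 3.1 itself doubts that a questionnaire alone would succeed. The expectation in 11.2 therefore rests on the randomised part.

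A reader might also infer that the split wastes a fixed quarter to a third of the information, or that a continuous term should replace it. Neither is supported. The loss depends on a graded effect that the protocol does not assume, and its talk of a limit suggests something closer to a step. For a step at 25 the split is the better test.

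Finally, a continuous term may sit in an analysis plan that is not shown, and its absence from the protocol is not in itself a fault. What remains is that the form the protocol does fix and power cannot support the statement in 11.2.

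**Conclusion.** The point holds as a modest, inexpensive improvement. The interaction fixed in section 8 can show a difference across 25 µg/l but cannot place a limit. With a 1.5-point step and ferritin assumed uniform from 5 to 50, it is significant in 32% of trials for a step at 15, 61% at 20, 85% at 25, 66% at 30 and 43% at 35. If the effect is graded, the split keeps about 63 to 75% of the information in the cases listed (less under some log-linear shapes), so 85% power becomes about 93 to 96.5% with the continuous value. If the effect is a step at 25, the loss is nil and a linear term is worse, 73% against 85%. The stated power is right, and the primary analysis and its error rate are not touched.

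**What to change.** In section 8, keep the planned and powered interaction test at 25. Add two prespecified items, fixed before unblinding:

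- a treatment by continuous (log) screening ferritin interaction;
- the estimated treatment effect with its confidence band across the observed ferritin range, for example from a spline with three knots.

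State that any remark about a ferritin limit will rest on the curve and its band rather than on the split, and that the band will be wide relative to 1 point. If this is not wanted, soften the sentence in section 11.2. When editing, also reconcile the class boundary: section 4.6 places exactly 25 in the lower class at screening, section 8 places it in the upper class at baseline, and sections 3.3.3 and 4.3.2 place it in neither.

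The cost is a few lines of code and one figure, with no new data. The drawback is one more secondary analysis, which should be labelled supportive so that it does not become an uncontrolled claim.
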